# Comparison of 75 mg versus 150 mg aspirin for the prevention of preterm preeclampsia in high-risk women at a tertiary level hospital: study protocol for a randomized double-blind clinical trial

**DOI:** 10.1186/s13063-024-08520-z

**Published:** 2024-10-15

**Keywords:** Aspirin prophylaxis, Clinical trial, Fetal outcomes, High-Risk women, Hypertensive disorders of pregnancy, Maternal outcomes, Obstetric care, Pre-Eclampsia, Preterm pre-Eclampsia, Evidence-Based practice

## Abstract

**Background:**

Hypertensive disorders of pregnancy (HDP) pose significant risks to maternal and fetal health, with substantial mortality and morbidity rates globally, particularly in developing countries. Pre-eclampsia (PE) accounts for a notable portion of maternal morbidity and mortality, with varied prevalence across regions within countries like India. Despite advancements, disparities in healthcare access persist, influencing outcomes. PE not only affects maternal health during pregnancy but also predisposes women to long-term cardiovascular complications, emphasizing the need for early screening and preventive measures.

**Methods:**

This prospective randomized double-blind clinical trial aims to compare the efficacy and safety of 75 mg versus 150 mg aspirin for preventing preterm pre-eclampsia in high-risk women. Screen-positive women aged 18–45 years with singleton pregnancies between 12 and 16 weeks of gestational age will be enrolled. They will be randomized in a 1:1 ratio to receive either 75 mg or 150 mg of aspirin nightly until 37 weeks of pregnancy or earlier if preterm pre-eclampsia develops. Feto-maternal outcomes, including preterm pre-eclampsia incidence and neonatal and maternal complications, will be assessed. The sample size calculation based on expected proportions of preterm pre-eclampsia in both groups indicates a total of 370 participants (185 per group) accounting for 20% attrition.

**Discussion:**

This prospective randomized double-blind clinical trial aims to compare the effectiveness and safety of two doses of aspirin (75 mg vs 150 mg) in preventing preterm pre-eclampsia in high-risk women. The potential implications of this study are significant, including the optimization of aspirin prophylaxis, the development of evidence-based guidelines, and comprehensive assessment of maternal and fetal outcomes. In conclusion, the results of this study have the potential to significantly impact clinical practice by enhancing maternal and perinatal health outcomes and contributing to evidence-based obstetric care.

**Trial registration:**

Clinical Trials Registry-India CTRI/2023/12/060983. Trial was registered prospectively on 29 December 2023. Acknowledgement Number REF/2023/12/076358. https://acrobat.adobe.com/id/urn:aaid:sc:AP:15870322-f1f4-4460-900c-6e056ab83a44.

**Supplementary Information:**

The online version contains supplementary material available at 10.1186/s13063-024-08520-z.

## Introduction

Hypertensive disorders of pregnancy (HDP) are a major health problem worldwide, accounting for 500, 000 fetal deaths and 70,000 maternal deaths, and of these, every year, 40,000 maternal deaths are from developing countries [1]. Globally hypertensive disorders of pregnancy and chronic hypertension affect approximately 10% and 1.5% of pregnant women, respectively, with serious fetal and maternal implications [2].

Pre-eclampsia (PE) affects 5–7% of all pregnancies and along with eclampsia is the major contributor to maternal morbidity and 10–15% of maternal mortality and also perinatal mortality. In India, the prevalence of HDP and pre-eclampsia is 9% and 3–6%, respectively, contributing to 18.35% of maternal morbidity [3].

The highest prevalence from India is reported in southern India (Lakshadweep—65.88% and Kerala—61.16%) and western India (Goa—63.38%) and lowest in Eastern India (Nagaland 2.36%), which may be due to the difference in antenatal coverage of these states. A study from South India reported that hypertension complicates 10.3% of pregnancies in northwest Karnataka [4]. There are disparities within India in access to health care and death rates due to HDP, which vary across states and also between urban and rural populations [5].

A systematic review, including mostly cross-sectional studies from southern India, showed high pooled prevalence of HDP of 11% (95% confidence interval, 5–17%), i.e., 1 out of 11 women suffers from it. Hence, it is the need of the hour to implement early screening for HDP through focused attention of policy makers and healthcare professionals [3]. An Indian study similarly found that the incidence of eclampsia is 1.5%, and there is no reduction in it and perinatal mortality rate over the last few decades, although there is a slight decline in maternal mortality [6].

Delivery resolves most signs and symptoms of PE but persistent postpartum pre-eclampsia is associated with risk for short-term and long-term cardiovascular and cerebrovascular morbidity. These women are predisposed to an increased risk of peripartum cardiomyopathy (PPCM) that can progress to chronic heart failure, which may lead to death.

Women with a history of HDP especially high diastolic blood pressure have two to three times higher risk of cardiovascular mortality compared to that of women with normal blood pressure during pregnancy, needing individualized cardiovascular follow-up to reduce their risk of mortality due to cardiovascular event [7]. PE is also associated with a fourfold increase in future heart failure and twofold increase in coronary heart disease, stroke, and death due to CHD [8].

Multiple episodes of pre-eclampsia and its increasing severity escalates future risk of cardiovascular disease. A study demonstrated that the odds of a fatal outcome from cardiovascular disease were greater than the odds of diagnosis which meant that women may die from the sequelae even without diagnosis of cardiovascular disease. Later in life, these women had 4.7-fold, fourfold, and threefold increased risk for subsequent end-stage renal disease, stroke, and vascular dementia, respectively [9]. It has been advocated that there is an urgent need for uniform guidelines and their implementation to improve the health of women with a history of PE. This can be done by making the public aware about the cardiovascular risk associated with it and by promoting a cardiovascular prevention program [10].

PE is a double-edged sword and adversely affects the newborn as well, leading to increased neonatal morbidity and mortality which may be due to iatrogenic prematurity, fetal growth restriction (FGR), and abruptio placentae [11]. An increased incidence of bronchopulmonary dysplasia and retinopathy of prematurity has also been reported in neonates due to extreme prematurity. About 80% of pre-eclampsia cost is due to preterm pre-eclampsia, leading to iatrogenic prematurity (≤ 37 weeks). The cost burden of pre-eclampsia per infant is estimated to range from $150,000 at 26 weeks gestational age reducing to $1311 at 36 weeks gestational age [12]. Children born to women with pre-eclampsia in their teenage years and beyond have an increased risk of cardiovascular disease and pulmonary hypertension [11].

The various clinical risk factors for PE are teenage pregnancy, primigravida, multiple gestation, history of diabetes, pre-existing hypertension, obesity, and previous history of HDP [13, 14]. NICE recommends screening for PE based on maternal characteristics along with medical, obstetric, and family history, which has a detection of 40% and 33% for preterm and term pre-eclampsia, respectively at a screen-positive rate of 11%. First-trimester quad was done at 11–13 + 6 weeks using maternal characteristics along with MAP, PIGF, and PAPP-A with/without UTPI and has a detection rate of 76% and 38% for preterm and term pre-eclampsia, respectively, at a FPR of 10% [11].

Preterm pre-eclampsia is due to defective placentation and low-dose aspirin (LDA) when started between 12 and 16 weeks of pregnancy corrects the imbalances in the levels of thromboxane A2 and prostacyclin, maintaining adequate uteroplacental blood supply. So aspirin improves defective placentation without increasing the risks of adverse maternal and perinatal outcomes [15].

Early prediction and prevention of pre-eclampsia would greatly contribute to improved maternal and perinatal health. Prevention of iatrogenic prematurity due to preterm PE is a very cost-effective measure. Aspirin is an inexpensive and widely available drug that has the potential to safely prevent preterm PE, resulting in reduced maternal and fetal morbidity and mortality [16]. Low-dose aspirin prophylaxis to prevent preterm pre-eclampsia is now recommended till 37 weeks of pregnancy in high-risk women [13].

Although low-dose aspirin has a good maternal and fetal safety profile, some authors have reported a higher incidence of intrapartum bleeding (2.9% aspirin users vs 1.5% nonusers), postpartum hemorrhage (10.2% vs 7.8%), postpartum hematoma (0.4% vs 0.1%), and neonatal intracranial hemorrhage (0.07% vs 0.01%) in aspirin users. A higher incidence of bleeding among aspirin users was present for those who had a vaginal birth but not those who had a cesarean delivery [15].

While numerous randomized trials have investigated the prophylactic use of aspirin in the prevention of pre-eclampsia, the optimal dose still remains unclear. Prediction of preterm PE in the first trimester enables the caregiver in preventing this deadly disease using aspirin. All “at risk” women should be started with low-dose aspirin and earlier studies have used 75–81–100–150 mg [17–19]. The safety of 150 mg of aspirin needs to be validated and the minimum most effective dose for the prevention of preterm PE should be used. Hence, there is an urgent need for more evidence-based studies to resolve this dilemma about the appropriate dose of aspirin prophylaxis, weighing the benefit versus harm of aspirin.

Hence, this prospective randomized double-blind clinical trial is being carried out to compare 75 mg versus 150 mg Aspirin for the prevention of preterm pre-eclampsia in high-risk, screen-positive women.

## Summary of relevant studies

### Systematic reviews and *meta*-analyses

A systematic review including 23 randomized controlled trials (RCTs) with a total of 26,952 participants examined the impact of LDA on pre-eclampsia. The review found that aspirin dosages ranged from 50 mg/day to 150 mg/day. In participants at increased risk for pre-eclampsia, the incidence of pre-eclampsia varied from 4 to 30%. The use of LDA was significantly associated with a lower risk of pre-eclampsia, perinatal mortality, preterm birth, and fetal growth restriction (FGR). However, the review found no significant increase in postpartum or other bleeding-related harms nor long-term harms. The absolute risk reductions for pre-eclampsia with aspirin ranged from 1 to 6% in larger trials, while the reductions in perinatal morbidity ranged from 0.5% to 1.1% in the largest trials [20].

The USPSTF concluded with moderate certainty that daily low-dose aspirin (81 mg) is beneficial for reducing the risk of pre-eclampsia, preterm birth, small-for-gestational-age, and perinatal mortality in high-risk pregnant individuals. This led to their recommendation of low-dose aspirin prophylaxis for high-risk women starting after 12 weeks of gestation [14].

### Recent studies and trials

A recent study conducted in China compared the effects of a placebo versus 75 mg daily LDA on pre-eclampsia incidence. The results indicated that 10.43% of women in the LDA group and 22.52% in the control group developed pre-eclampsia. The odds ratio for developing pre-eclampsia with LDA was 0.40 (95% CI = 0.20–0.82, *P*= 0.0098), suggesting a significant benefit of aspirin prophylaxis [21].

Wright and colleagues found that aspirin reduced the length of stay in neonatal intensive care units by approximately 70%, primarily due to a decrease in the rate of iatrogenic prematurity at < 32 weeks gestation, related to early prevention of pre-eclampsia. This reduction in NICU stay was associated with implications for both short-term and long-term healthcare costs and infant survival [22].

### Effectiveness in specific populations

A multicenter, double-blind, randomized placebo-controlled trial assessed 1776 women at high risk for preterm pre-eclampsia. Participants received either 150 mg daily aspirin or placebo from 11 to 14 weeks of gestation until 36 weeks. Preterm pre-eclampsia rates were 1.6% in the aspirin group and 4.3% in the placebo group. The study concluded that low-dose aspirin effectively prevents preterm pre-eclampsia [23].

Rolnik and colleagues conducted the ASPRE trial, involving 26,941 singleton pregnancies, to screen for preterm pre-eclampsia using a combined algorithm of maternal factors and biomarkers. Women with a preterm pre-eclampsia risk > 1 in 100 were assigned to receive 150 mg daily aspirin or placebo from 11–14 weeks until 36 weeks. The study showed a 62% reduction in preterm pre-eclampsia incidence with aspirin [23].

### Gaps in current knowledge

Despite the evidence supporting aspirin’s efficacy in preventing pre-eclampsia, several uncertainties remain. One key issue is the optimal dosage and timing, as there is no clear consensus on the most effective dose. While 75 mg and 150 mg are commonly prescribed, debate persists regarding their comparative effectiveness. Additionally, the long-term effects of aspirin on infants exposed during pregnancy are underexplored, with most research focusing on short-term outcomes and leaving a gap in understanding potential neurodevelopmental and health consequences later in life. Another challenge lies in risk stratification, as identifying women at highest risk for pre-eclampsia who would benefit most from aspirin prophylaxis remains difficult, and current criteria may not fully optimize treatment outcomes.

### Research question and justification

The primary objective of this study is to evaluate the efficacy and safety of two different dosages of low-dose aspirin (LDA), 75 mg and 150 mg daily, in preventing preterm pre-eclampsia in high-risk pregnant women. While LDA has been widely used and studied, the optimal dosage remains uncertain. Previous research indicates that aspirin can lower the incidence of preterm pre-eclampsia and its complications, but there is variability in the effectiveness of different dosages and timing of initiation.

### Need for the study

This study aims to address these gaps by comparing the effectiveness of 75 mg and 150 mg daily aspirin in preventing pre-eclampsia among high-risk pregnant women. By refining dosage guidelines, this research will help tailor preventive strategies more effectively and potentially improve maternal and fetal outcomes. Additionally, it will provide valuable insights into the long-term effects of aspirin on infant health, contributing to a more comprehensive understanding of its benefits and risks.

## Aims and objectives

### Aim

To compare 75 mg versus 150 mg aspirin for the prevention of preterm preeclampsia in high-risk women.

### Objective

#### Primary objective

To compare 75 mg versus 150 mg aspirin for the prevention of preterm preeclampsia in high-risk women.

#### Secondary objectives

To evaluate feto-maternal outcomes in high-risk women receiving 75 mg versus 150 mg aspirin for the prevention of preterm preeclampsia.To compare the side effects of 75 mg versus 150 mg aspirin during pregnancy.

#### Rationale/gaps in existing knowledge

Lack of evidence about (i) optimum dose of aspirin, 75 versus 150 mg, for the prevention of preterm PE and (ii) when to start and stop aspirin during pregnancy for the prevention of preterm PE.

##### Novelty

No international or Indian prospective randomized double-blind interventional trial comparing 75 mg versus 150 mg aspirin for the prevention of preterm PE in high-risk/screen-positive women.

##### Research question

Is aspirin in dose of 150 mg better than 75 mg in the prevention of preterm preeclampsia in high-risk women?

##### Hypothesis

Aspirin in dose of 150 mg is better than 75 mg in the prevention of preterm preeclampsia in high-risk women.

## Material and methods

Include objective-wise work plan under the following sub-headings.

AStudy design—prospective randomized double blind clinical trialBStudy site—Department of Obstetric & Gynecology, Pathology, Biochemistry & SPM**,** VMMC & Safdarjung Hospital, New DelhiCMethods—(e.g., PICO)

### Population

All women 18–45 years attending ANC and Fetal Medicine OPD of VMMC & Safdarjung Hospital between 11 and 13 + 6 weeks of gestational age will be screened for high risk for preterm PE using the first-trimester quadruple testing (1 T Quad). Women with a risk for preterm PE 1:100 and greater will be labeled as screen positive or high risk. 1 T Quad will be done using Perkin Elmer LifeCycle 7.0 software on Victor 2D Instrument (Time Resolved Fluorescence—DELFIA).

### Inclusion criteria

Women 18–45 years of age with singleton pregnancy 12–16 weeks of POG were found to be screen-positive for preterm preeclampsia in the first trimester by 1 T Quad test.

### Exclusion criteria

Hypersensitivity to aspirin or other NSAIDsActive peptic ulcer diseaseActive bleeding in pregnancy:Threatened miscarriageExpanding retroplacental hematomaAPHSevere liver diseaseMother on anticoagulant or anti-platelet drugsUnderlying bleeding disorder in mother:Von Willebrand diseaseImmune thrombocytopenia purpura (ITP)Factor VIII deficiency (hemophilia)Severe gestational thrombocytopenia (platelet count < 100,000 × 10.^9^/L)Fetus diagnosed with malformation or aneuploidy

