#### Proteinuria

300 mg or more per 24-h urine collection orProtein/creatinine ratio of 0.3 mg/dL or more orDipstick reading of 2 + (used only if other quantitative methods not available) or in the absence of proteinuria, new-onset hypertension with the new onset of any of the following:Thrombocytopenia: platelet count less than 100,000 10^9^/LRenal insufficiency: serum creatinine concentrations greater than 1.1 mg/dL or a doubling of the serum creatinine concentration in the absence of other renal diseaseImpaired liver function: elevated blood concentration of liver transaminases to twice normal concentrationPulmonary edemaNew-onset headache unresponsive to medication and not accounted for by alternative diagnoses or visual symptoms

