#### Preeclampsia with severe features

Systolic blood pressure of 160 mm Hg or more or diastolic blood pressure of 110 mm Hg or more on two occasions at least 4 h apart (unless antihypertensive therapy is initiated before this time)Thrombocytopenia (platelet count less than 100,000 10.^9^/L)Impaired liver function that is not accounted for by alternative diagnoses and as indicated by abnormally elevated blood concentrations of liver enzymes (to more than twice the upper limit normal concentrations) or by severe persistent right upper quadrant or epigastric pain unresponsive to medicationsRenal insufficiency (serum creatinine concentration of more than 1.1 mg/dL or a doubling of the serum creatinine concentration in the absence of other renal disease)Pulmonary edemaNew-onset headache unresponsive to medication and not accounted for by alternative diagnosesVisual disturbances

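### The platelet threshold pairs 100,000 with the unit 10^9/L in the exclusion criterion and twice in the preeclampsia criteria; number and unit do not match, so the printed cut-off cannot discriminate

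*Protocol article*

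**What the plan says.** The protocol article gives a platelet threshold in three places.

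- **Exclusion criteria:** "Severe gestational thrombocytopenia (platelet count < 100,000 × 10.^9^/L". This is the only exclusion in the list that carries a laboratory number.
- **Diagnostic criteria for preeclampsia, Proteinuria:** a woman can be diagnosed without proteinuria under the rule "in the absence of proteinuria, new-onset hypertension with the new onset of any of the following". Thrombocytopenia heads the list that follows, again with 100,000 and the unit 10^9/L, here without a multiplication sign.
- **Preeclampsia with severe features:** "Thrombocytopenia (platelet count less than 100,000 10.^9^/L".

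The number of women developing preterm preeclampsia in each arm is the primary outcome (Primary outcomes). Gestational hypertension is listed separately among the secondary outcomes. Onset of preterm preeclampsia also ends study treatment (Method of administration of investigational products).

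**The concern.** A platelet count can be expressed per microlitre or in multiples of 10^9 per litre. The two scales differ by a factor of 1000, and the article joins a number of the size used on the first scale to the unit of the second. No section states the threshold in another way that would settle which part is wrong.

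The figure has two jobs. It is an entry criterion in a comparison of two doses of an antiplatelet drug, with bleeding among the outcomes. It is also one of the features that turns new hypertension without proteinuria into preeclampsia, and so helps to separate the primary outcome from gestational hypertension. A threshold that every count falls below can do neither job. Whoever applies it must replace the printed number with another, and the document does not say with which.

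**Working it through.** **Inputs**

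- Printed threshold: 100,000 × 10^9/L (Exclusion criteria; the same number and unit under Proteinuria and under Preeclampsia with severe features).
- Conversion: 1 L = 10^6 µL.
- Range of human platelet counts: not in the documents. Assumed to be about 150 to 450 × 10^9/L, and checked over the wider range 50 to 2000 × 10^9/L.

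**Step 1. The printed value**

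100,000 × 10^9/L = 10^5 × 10^9/L = 10^14/L.
10^14/L ÷ 10^6 µL/L = 10^8 per µL, or 100 million per µL.

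**Step 2. The value if 100,000 is meant per microlitre**

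100,000/µL × 10^6 µL/L = 10^11/L = 100 × 10^9/L.

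**Step 3. Ratio**

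10^14 ÷ 10^11 = 1000.

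**Step 4. Can the printed figure discriminate?**

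| Count (× 10^9/L) | Share of printed threshold | Below it? |
|---|---|---|
| 50 | 0.05% | yes |
| 100 | 0.10% | yes |
| 150 | 0.15% | yes |
| 450 | 0.45% | yes |
| 1000 | 1% | yes |
| 2000 | 2% | yes |

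Every count in the range satisfies the inequality, so the number carries no information about the woman.

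**Step 5. Effect on the diagnostic limb**

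Under Proteinuria the listed feature must itself be of new onset. If every count is below the printed figure at all times, there are two literal readings. Judged on the count alone, the limb is always met. Judged on new onset, it is never met, because the woman was already below the figure before her blood pressure rose. The limb fails to discriminate under either reading.

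**Step 6. Does any design figure depend on it?**

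No. The Sample size section uses 17% and 6.5%, two-sided α = 0.05 and 80% power. Its formula reproduces 147 per group. 2 × 147 = 294, and 294 ÷ 0.8 = 367.5, or 368, against the stated 370 (185 per group). The platelet threshold does not enter.

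**The case against.** The strongest reply is that this is a slip of notation with no practical force. Much of that stands.

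- **The exclusion names a condition.** A reader might infer from the number that every woman is excluded. The text does not support that: it lists severe gestational thrombocytopenia, with the count in brackets as its definition. A woman with an ordinary count does not have that condition, and trained staff would probably see what was meant. The principal investigator also gives final approval of eligibility, and the article reports that screening began on 1 May 2024.
- **Gestational hypertension would not all become preeclampsia.** A reader might infer this from the criteria without proteinuria. The new-onset wording stands against it, as step 5 shows.
- **Divergence between sites is not documented.** The article names one hospital. The Discussion says only that more recruitment sites may be needed.
- **No automated check is described.** The case report form is not shown, and its completion rules describe entries in black ink, so nothing indicates that the literal number would be applied mechanically.
- **The three places agree with one another.** The document does not contradict itself on the printed figure.

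These points limit the consequences but do not make the figure right. The stray dot in the exponent is probably damage from text extraction. The pairing of 100,000 with 10^9/L is not explained that way: it occurs in three places, and under Proteinuria the dot is absent. Nor is this a detail left to a fuller document, since the article states the value. The agreement of the three places means that none of them can be used to correct the others.

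**Conclusion.** The point holds as an error of number and unit. The printed threshold is 10^8 per microlitre, 1000 times the value if 100,000 per microlitre is meant. As a number it cannot discriminate for eligibility or for the thrombocytopenia limb of the definition on which the primary outcome rests.

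The likely effect on conduct is small, because the named condition makes the purpose recognisable. The documents do not show that enrolment would stop or that outcomes would be misclassified wholesale. Sample size, power and type I error are unaffected. It still deserves correction, because it sits in an entry criterion and in an outcome definition rather than in background text.

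The conclusion rests on two assumptions. The factor of 1000 takes 100,000 to be meant per microlitre, which the documents do not state. The statement that every count lies below the printed figure uses an assumed range of 50 to 2000 × 10^9/L; even the top of that range reaches only 2% of the figure.

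**What to change.** The sponsor should confirm the intended threshold and restate it with a matching number and unit in all three places: Exclusion criteria, the thrombocytopenia item under Proteinuria, and Preeclampsia with severe features. For the conversion only, 100,000 per microlitre equals 100 × 10^9/L; which value is intended is for the sponsor to say.

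The case report form entries for eligibility and for the preeclampsia outcome should carry the same number and unit as the corrected text.

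The cost is three corrected lines and a check of the form. Nothing in the design or the sample size has to change.
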